### Assessment of recurrence

The recurrence will be assessed by clinical follow-up at 1, 3, 6, 9, and 12 months with 12-lead ECG + 24 Holter monitoring. Transthoracic echocardiography will be also performed to record the presence of an atrial contraction in case of sinus rhythm. Quality of life will be assessed by a modified 36-item Short Form Health Survey and the Euro 5D questionnaire. The primary outcomes include the freedom from AF at 12 months, as detected by a 12-lead ECG and a 24-hour Holter examination after 3, 6, and 9 months of follow-up, and the occurrence of a second ablation procedure. The secondary outcomes include the duration of the procedures, freedom from any documented atrial arrhythmia, incidence of procedural complications, any late complication related to the procedures, and quality of life.

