**Methods/Design:**

This is a controlled (2:1) randomized trial comparing use of a percutaneous catheter with minimally invasive transthoracic surgical ablation of persistent atrial fibrillation. The inclusion and exclusion criteria, definitions, and treatment protocols are those reported by the 2012 Expert Consensus Statement on catheter and surgical ablation of atrial fibrillation. Patients will be randomized to either percutaneous catheter (*n* = 100) or surgical (*n* = 50) ablation as the first procedure. After 3 months, they are re-evaluated, according to the same guidelines, and receive a second procedure if necessary. Crossover will be allowed and data analyzed on an “intention-to-treat” basis. Primary outcomes are the incidence of sinus rhythm at 6 and 12 months and the proportions of patients requiring a second procedure.

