### Statistical analysis

Randomization will be performed by using currently available computer software. Sample size is based on the hypothesis that the success rate of the first procedure will be approximately 70% for the surgical cases and 35% to 40% for the PCA cases. At the end of the interventions, the number of patients in SR should be equivalent in the two groups, whereas the proportions of those submitted to a second procedure, either percutaneous or surgical, should differ significantly. Variables will be analyzed with an intention-to-treat method. The three possible results of this study are described in Table 1. A flow chart depicting the most favorable result in which the power of the test is 98% is shown in Figure 1. Data will be expressed as mean ± SD and 95% confidence limits, as appropriate. Comparisons between patient groups will be performed with the Mann–Whitney test for continuous variables and the χ^2^ test for categoric variables. The *z* test and the odds ratio will be used for differences between proportions of patients receiving repeated procedures in the two groups. A value of *P* < 0.05 will be considered statistically significant. Time-to-event distributions will be estimated by the Kaplan-Meier method and compared with the log-rank test. The Cox proportional hazards model will be used to identify independent risk factors for recurrences. Stepwise selection procedure will be adopted. A value of *P* < 0.05 will be considered significant for variable entry for stepwise selection. Analyses are performed with the SPSS 18.0 software package (SPSS, Inc, Chicago, IL, USA).

**Table 1 T1:** Anticipated results for different success rates of first PCA procedure

**% of SR in the PCA group after first procedure**	**35%**	**45%**	**50%**
**χ**^ **2 ** ^**test for first procedure**	*P* < 0.0001	*P* = 0.007	*P* = 0.03
Power of the test	99%	84%	65%

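### Quality of life would be compared more precisely with a pre-randomisation score and baseline-adjusted analysis than with the unadjusted Mann–Whitney test, the only test the article names for continuous variables

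*Protocol article*

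**What the plan says.** Under Assessment of recurrence, the protocol article names the instruments: "Quality of life will be assessed by a modified 36-item Short Form Health Survey and the Euro 5D questionnaire". The closing list of secondary outcomes in that section ends with "any late complication related to the procedures, and quality of life".

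The only visit times in that section belong to rhythm monitoring: "The recurrence will be assessed by clinical follow-up at 1, 3, 6, 9, and 12 months with 12-lead ECG + 24 Holter monitoring". The quality-of-life sentence has no times of its own, and no baseline questionnaire is mentioned anywhere in the article.

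Under Statistical analysis, one general rule covers scores of this kind: "Comparisons between patient groups will be performed with the Mann–Whitney test for continuous variables and the χ^2^ test for categoric variables". It does not mention quality of life, and it does not say whether follow-up scores or changes would be compared. The one covariate model named, a Cox model with stepwise selection, is for recurrence. The threshold is "A value of *P* < 0.05 will be considered statistically significant".

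Allocation is unequal: "Patients will be randomized to either percutaneous catheter (*n* = 100) or surgical (*n* = 50) ablation as the first procedure". No effect size, SD, correlation or power is given for quality of life.

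**The concern.** A patient's own earlier score is usually a strong predictor of a later score on the same questionnaire. A two-group rank test takes no covariate, so the variation a baseline score could explain stays in the comparison as noise. The smaller arm has only 50 patients and the article makes no power claim for this outcome, so precision matters.

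The Statistical analysis section expects similar numbers in sinus rhythm in both arms once all interventions are done. The article rests its case mainly on fewer second procedures. If rhythm does end up similar, quality of life and complications will also weigh in judging a surgical first step. An imprecise comparison could then leave a real difference in either direction undetected.

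**Working it through.** **1. The plan's own power figures.** Table 1 gives 99%, 84% and 65% for first-procedure success of 70% (surgical, n = 50) against 35%, 45% and 50% (PCA, n = 100). For 35%:

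- pooled rate = (35 + 35)/150 = 0.467
- null SE = √[0.467 × 0.533 × (1/100 + 1/50)] = 0.0864
- alternative SE = √[0.35 × 0.65/100 + 0.70 × 0.30/50] = 0.0805
- power = Φ[(0.35 − 1.96 × 0.0864)/0.0805] = 98.8%

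The same formula gives 83.8% and 65.1% for the other two columns. The figures reproduce, but they concern first-procedure success and say nothing about quality of life.

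**2. Inputs for quality of life.**

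- From the article: 100 and 50 patients, and a 0.05 threshold (taken as two-sided).
- Assumed: standardised difference d = 0.4 SD (range 0.2 to 0.6), correlation r = 0.4 to 0.6, normal scores, no dropout, and a baseline score for every patient.

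**3. Variance.** ANCOVA multiplies the residual variance by 1 − r², giving 0.84, 0.75 and 0.64. The reductions are 16%, 25% and 36%, whatever the value of d. At r = 0.5 this is worth 1/0.75 = 1.33 times the patients.

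**4. Power at d = 0.4.** The SE of a difference in SD units is √(1/100 + 1/50) = 0.1732.

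- Mann–Whitney, with relative efficiency 0.955 under normality: Φ(0.4 × √0.955/0.1732 − 1.96) = Φ(0.297) = 61.7%. Simulation (20,000 runs) gives 60.6%.
- Unadjusted t-test (noncentral t): 63.1%.
- ANCOVA at r = 0.5: Φ[0.4/(0.1732 × √0.75) − 1.96] = Φ(0.707) = 76.0%.
- ANCOVA at r = 0.4, 0.5 and 0.6: noncentral t gives 70.7%, 75.5% and 81.8%; simulation (10,000 runs each) gives 70.4%, 75.7% and 81.6%.

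So about 2 points of the gain come from leaving the rank test under normal data. The rest, about 8 to 19 points, comes from the adjustment.

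**5. Range over d** (power in %; Mann–Whitney by the approximation, the rest by noncentral t):

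| d | Mann–Whitney | t-test | ANCOVA r = 0.4 | r = 0.5 | r = 0.6 |
|---|---|---|---|---|---|
| 0.2 | 20.3 | 20.9 | 24.0 | 26.3 | 30.0 |
| 0.3 | 39.5 | 40.6 | 46.7 | 51.1 | 57.6 |
| 0.4 | 61.7 | 63.1 | 70.7 | 75.5 | 81.8 |
| 0.5 | 80.5 | 81.8 | 87.9 | 91.2 | 94.8 |
| 0.6 | 92.3 | 93.1 | 96.4 | 97.8 | 99.0 |

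The gain over Mann–Whitney is smallest at d = 0.2 and d = 0.6 with r = 0.4 (about 4 points). It is largest at d = 0.4 with r = 0.6 (81.8 − 61.7 = 20 points, or 21 against the simulated 60.6).

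**6. If change scores were meant.** The variance of a change is 2 − 2r in units of the score variance. At d = 0.4, a normal-theory comparison of changes has 56%, 64% and 73% power at r = 0.4, 0.5 and 0.6. ANCOVA by the same normal formula has 71%, 76% and 82%. Change scores therefore also fall short of ANCOVA, and they too need a baseline.

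**7. Missing baselines.** If a fraction f of patients lack a baseline at random and receive the mean, the variance reduction falls to about (1 − f)r². With an assumed f = 0.5 and r = 0.5 it is 0.5 × 0.25 = 12.5%. Power at d = 0.4 is then Φ[0.4/(0.1732 × √0.875) − 1.96] = Φ(0.509), about 69%.

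**The case against.** The strongest reply is that nothing here is wrong. Under randomisation an unadjusted Mann–Whitney test is valid, because chance baseline imbalance is already allowed for in its error rate. Quality of life is a secondary outcome with no power claim. The article is condensed, so the full protocol may well schedule a baseline questionnaire. All of this stands, and it limits the point to efficiency. It does not remove the point, because the article does state a method for continuous variables and that method cannot adjust.

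Some stronger readings are tempting, but the documents do not support them:

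- A reader might infer that quality of life is measured only after treatment. The listed visits are stated for recurrence; for quality of life the article gives no times at all.
- A reader might infer that follow-up scores are compared without regard to baseline. The article does not say, and a rank test could be applied to changes.
- A reader might infer that only a P value would be reported. The same section plans means with SDs and 95% confidence limits where appropriate, though it does not expressly promise an interval for the between-arm difference.
- A reader might infer that an altered SF-36 cannot be scored in the standard way. The alteration is not described, and an article may leave that detail to the full protocol.

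The calculations also assume normal scores, which favours the linear model. Skewed or bounded scores were not examined, so the roughly 2 points gained by leaving the rank test should not be relied on.

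**Conclusion.** The point holds as a cheap improvement to a secondary analysis. The one test stated for continuous variables is valid but cannot use a baseline score, and no baseline quality-of-life assessment is mentioned.

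The firmest result is the r² reduction in residual variance, which does not depend on the treatment effect. The power figures are illustrations: d and r are assumptions, and unadjusted power itself runs from about 20% to 92% over the range of d shown. They are also upper values for this trial. Under Trial status the article reports that recruitment was under way at submission, so some patients may have no baseline score. The documents do not support calling the planned comparison biased or invalid.

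**What to change.** - Have patients complete the questionnaires already in use once before randomisation, so that knowledge of the allocation cannot affect the baseline answers.
- For quality of life, replace the Mann–Whitney test by ANCOVA of the 12-month score on arm and baseline score. Report the adjusted mean difference with its 95% CI. Twelve months is proposed because it is the last follow-up visit listed.
- Keep patients already enrolled without a baseline score in the analysis, using mean imputation of the baseline covariate. This is for the covariate only, not for a missing outcome.

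The cost is one extra questionnaire completion per new patient and one line in the analysis plan. The gain shrinks with the share of patients who have no baseline score. If the full protocol already collects a baseline score, only the change of analysis is needed.

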In the present trial, we examine the hypothesis that a staged approach involving minimally invasive surgical ablation of persistent atrial fibrillation, followed by a second percutaneous procedure in cases of recurrence, will have a success rate at 12 months higher than repeated percutaneous procedures. According to the recently published European guidelines on surgical ablation of AF alone, we will select patients with a class IIb indication to surgery and use the class I bipolar radiofrequency as the energy source for the ablation [12].

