### Staged surgical ablation group

Fifty patients will be randomized to surgical ablation of AF. The ablation procedure will be performed with the use of Estech cobra fusion, according to the manufacturer’s instructions and to the commonly described techniques [10,12,15]. Up to three applications will be allowed to ablate the left atrial box. Bidirectional block will be checked, and reasons for not obtaining it will be noted. Inducibility of AF at the end of the procedure will be recorded. Cardioversion will be allowed to restore SR. At the end of the procedure, the patient will be awakened and transferred to the ward. An interval of 3 months will be allowed after the initial ablation procedure, as per the Heart and Rhythm European Society Association/European Heart Rhythm Association/European Cardiac Arrhythmia Society expert consensus statement [13]. During this period, the recurrences of AF, atrial tachycardias, and atrial flutter will not be counted toward the primary or secondary end points. Antiarrhythmic medications may be continued for the first 3 months to avoid early recurrences. At 3 months, they must be stopped to assess recurrences. For patients continuing to have recurrence controlled by the therapy, it will be left to the preference of the investigator to continue the medical therapy or to refer the patient for a PCA.

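### The primary rhythm outcome is defined in two conflicting ways, and the Methods version leaves out the 12-month examination, includes the 3-month one, and does not say how rhythm after a second procedure counts

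*Protocol article*

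**What the plan says.** The protocol article states its primary outcomes twice.

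- Abstract, Methods/Design: "Primary outcomes are the incidence of sinus rhythm at 6 and 12 months and the proportions of patients requiring a second procedure".
- Methods, Assessment of recurrence: the rhythm outcome is "freedom from AF at 12 months, as detected by a 12-lead ECG and a 24-hour Holter examination after 3, 6, and 9 months", alongside the occurrence of a second ablation. Freedom from any atrial arrhythmia is listed there as a secondary outcome.

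Four other statements bear on how these are read.

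- **Visits.** Assessment of recurrence: "The recurrence will be assessed by clinical follow-up at 1, 3, 6, 9, and 12 months with 12-lead ECG + 24 Holter monitoring".
- **Blanking.** The surgical group section allows 3 months after the first ablation, during which "the recurrences of AF, atrial tachycardias, and atrial flutter will not be counted toward the primary or secondary end points". The PCA group section also names a 3-month blanking period. On antiarrhythmic drugs the surgical section says: "At 3 months, they must be stopped to assess recurrences".
- **Second procedure.** Abstract: "After 3 months, they are re-evaluated, according to the same guidelines, and receive a second procedure if necessary".
- **Aim.** The Background predicts that the staged approach, including its second percutaneous procedure, "will have a success rate at 12 months higher than repeated percutaneous procedures". The Statistical analysis section expects something else: "At the end of the interventions, the number of patients in SR should be equivalent in the two groups".

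**The concern.** A primary endpoint has to give one answer for each patient. Here it may not, for three reasons.

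1. **Two definitions.** A patient in atrial flutter or atrial tachycardia is free of AF but not in sinus rhythm. The time points also differ: 6 and 12 months in one place, and 12 months read from 3, 6 and 9 in the other.
2. **A rule at odds with its own schedule.** A 12-month outcome should use the 12-month examination, which is planned but not listed. The 3-month examination is listed, although it coincides with the end of blanking, the stopping of drugs and the decision on a second procedure.
3. **No rule for combining examinations.** Whether AF at any listed visit is failure, or only AF at one visit, decides whether a second procedure can affect the result.

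At stake is whether the rhythm comparison measures the first procedure or the whole strategy. The Background hypothesis is about the strategy; the sample size rests on the first procedure. If the choice is left open, it can be made after the results are known.

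**Working it through.** **Step 1. The definitions side by side.**

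| | Abstract | Methods |
|---|---|---|
| Rhythm state | sinus rhythm | no AF |
| Outcome time | 6 and 12 months | 12 months |
| Examinations named | none | 3, 6 and 9 months |
| 12-month examination | implied | scheduled, not listed |
| 3-month examination | not used | listed |

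If months were counted from the end of blanking, 3, 6 and 9 would become 3+3, 6+3 and 9+3, that is 6, 9 and 12. That would remove the visit problem, but the text does not say so, and the same section numbers follow-up as 1, 3, 6, 9 and 12.

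**Step 2. Two readings of the Methods rule, for a patient with AF at month 3 who then has a second procedure.**

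- Cumulative: the patient has failed before the second procedure, whatever it achieves. The endpoint becomes first-procedure success and cannot test the Background hypothesis.
- Status at the last listed visit: the second procedure is judged at 9 months, not 12.

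The text does not choose between them.

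**Step 3. Reproduce the stated power.** Inputs from the Statistical analysis section and Table 1: surgical success q = 0.70, PCA success p = 0.35, 0.45 or 0.50, with 100 PCA and 50 surgical patients. Alpha is 0.05; two-sided is assumed because the text does not say.

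Power = Φ[(|q − p| − 1.96·s0)/s1], with s0 = √[p̄(1−p̄)(1/100 + 1/50)], p̄ = (100p + 50q)/150, and s1 = √[p(1−p)/100 + q(1−q)/50].

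For p = 0.35: p̄ = 0.467, s0 = 0.0864, s1 = 0.0805; (0.35 − 0.1694)/0.0805 = 2.24; power 98.8%.

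| PCA first-procedure success | Recomputed | Table 1 |
|---|---|---|
| 35% | 98.8% | 99% |
| 45% | 83.8% | 84% |
| 50% | 65.1% | 65% |

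The 98% quoted in the text for the most favorable case also fits (98.0% with continuity correction). At 40%, the upper end of the planning range, power is 94.6%. All these figures concern first-procedure success.

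**Step 4. Rhythm at 12 months after all procedures.** The plan gives no success rate for a second procedure. Assume a rate r, equal in both arms, with every first failure re-treated. Then surgical = 0.70 + 0.30r and PCA = p + (1 − p)r. Power uses the same formula.

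| r (assumed) | p | Surgical | PCA | Difference | Power |
|---|---|---|---|---|---|
| 35% | 35% | 80.5% | 57.75% | 22.75 points | 81% |
| 35% | 40% | 80.5% | 61.0% | 19.5 points | 69% |
| 50% | 35% | 85.0% | 67.5% | 17.5 points | 64% |
| 50% | 40% | 85.0% | 70.0% | 15.0 points | 52% |
| 70% | 35% | 91.0% | 80.5% | 10.5 points | 37% |
| 70% | 40% | 91.0% | 82.0% | 9.0 points | 29% |

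**Step 5. Second procedures of the other type.** The plan lets PCA failures go to surgery. If all of them do, at 70%, the PCA arm reaches 0.35 + 0.65 × 0.70 = 80.5%. If surgical failures get PCA at 35%, the surgical arm reaches 0.70 + 0.30 × 0.35 = 80.5%. The difference is zero.

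**The case against.** The strongest reply is that the slip is small and other text shows what was meant. The PCA section counts a switch to rate control as a failed repeated procedure, and the Statistical analysis section speaks of sinus rhythm once the interventions are over. Both suggest that rhythm after a second procedure is meant to be judged. A second procedure soon after month 3 would be followed by the 6- and 9-month examinations.

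Much of this stands, and it limits the point in four ways.

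- A reader might infer that the Methods endpoint cannot measure success after a second procedure. That is true only on the cumulative reading, which the text does not state.
- A reader might take the 22.75-point difference in the first row of Step 4 as the plan's implied strategy effect. It is not: it rests on an assumed 35% repeat success and on every PCA failure having a second PCA. The difference can be zero (Step 5).
- A reader might conclude that flutter and tachycardia belong in the primary outcome. The Methods already place the any-arrhythmia outcome among the secondaries, so restricting the primary to AF looks deliberate. What is wrong is only that the abstract's rhythm state differs.
- A reader might object that the abstract's 6-month reading can fall within 3 months of a repeat. The documents set no blanking after a second procedure, so this breaks none of their rules.

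The reply does not remove the conflict between the two definitions, the missing 12-month examination, or the use of the examination at the blanking boundary. These are statements on the page, not details left to a fuller document.

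**Conclusion.** The point holds as an inconsistency in the primary endpoint that must be corrected. Two definitions conflict in rhythm state and time points. The Methods version excludes the one examination made at its own outcome time and includes one at the end of blanking. How success after a second procedure is measured is undefined; the documents do not support saying that it is unmeasurable.

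The choice of reading has a large effect. For first-procedure success at the plan's 70% versus 35% to 40%, power is 98.8% to 94.6%. For 12-month rhythm after all procedures it is about 81% down to 29%, with an expected difference of 22.75 down to 9 points, or zero under the Step 5 pattern. The second range depends on assumed repeat success of 35% to 70%, equal in both arms, re-treatment of every first failure, and a two-sided 5% test. It illustrates the consequence and is not a forecast. The plan's own expectation of equal sinus rhythm at the end points the same way: Table 1's power does not carry over to a strategy endpoint.

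**What to change.** State one definition and use it in both the abstract and Assessment of recurrence.

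1. **Strategy success:** rhythm on the 12-lead ECG and 24-hour Holter at the 12-month visit, whatever procedures were done. Drop the 3-month examination from the endpoint.
2. **First-procedure success, reported separately:** no recurrence at the 6-, 9- and 12-month visits and no repeat ablation. Say that the Table 1 power applies to this measure.
3. **Rhythm state:** use either freedom from AF or sinus rhythm in both places. Freedom from any atrial arrhythmia can stay secondary, as the Methods have it.

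**Cost:** amendment wording only, since every visit and test is already scheduled. The article reports that recruitment is under way, so the change should be made and dated before outcomes are examined. The real downside is that the stated power no longer covers the 12-month strategy endpoint, and the article should say so.

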### Statistical analysis

Randomization will be performed by using currently available computer software. Sample size is based on the hypothesis that the success rate of the first procedure will be approximately 70% for the surgical cases and 35% to 40% for the PCA cases. At the end of the interventions, the number of patients in SR should be equivalent in the two groups, whereas the proportions of those submitted to a second procedure, either percutaneous or surgical, should differ significantly. Variables will be analyzed with an intention-to-treat method. The three possible results of this study are described in Table 1. A flow chart depicting the most favorable result in which the power of the test is 98% is shown in Figure 1. Data will be expressed as mean ± SD and 95% confidence limits, as appropriate. Comparisons between patient groups will be performed with the Mann–Whitney test for continuous variables and the χ^2^ test for categoric variables. The *z* test and the odds ratio will be used for differences between proportions of patients receiving repeated procedures in the two groups. A value of *P* < 0.05 will be considered statistically significant. Time-to-event distributions will be estimated by the Kaplan-Meier method and compared with the log-rank test. The Cox proportional hazards model will be used to identify independent risk factors for recurrences. Stepwise selection procedure will be adopted. A value of *P* < 0.05 will be considered significant for variable entry for stepwise selection. Analyses are performed with the SPSS 18.0 software package (SPSS, Inc, Chicago, IL, USA).

**Table 1 T1:** Anticipated results for different success rates of first PCA procedure

**% of SR in the PCA group after first procedure**	**35%**	**45%**	**50%**
**χ**^ **2 ** ^**test for first procedure**	*P* < 0.0001	*P* = 0.007	*P* = 0.03
Power of the test	99%	84%	65%

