### Percutaneous catheter ablation group

One hundred patients will be randomized to PCA and treated according to the protocol of the referring center. In all cases, complete PVI must be at least attempted and confirmed by bidirectional block. The referring investigator can then add any of the current methods of PeAF treatment, including substrate modification with the infusion of isoproterenol to uncover non-PVI triggers and CFAE. Lines can be drawn at the discretion of the investigators. Inducibility of AF at the end of the procedure will be recorded. Cardioversion will be allowed to restore SR.

After the 3-month blanking period, it will be left to the investigator’s preference to refer the patients with PeAF recurrence to a second PCA procedure, surgical ablation, or switch to a rate-control approach. The latter will be counted as a failed repeated procedure.

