**Difference between proportions**			
Fraction of second procedures in the two groups	0.65-0.30	0.55-0.30	0.50-0.30
Difference between fractions	0.35	0.25	0.2
95% confidence interval of difference	0.1 to 0.5	0.1 to 0.4	0.0 to 0.3

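### Table 1's power is for first-procedure success, which is not a listed outcome; it carries over to second procedures only if every recurrence in both arms counts as one

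*Protocol article*

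**What the plan says.** **What is powered.** Statistical analysis: "Sample size is based on the hypothesis that the success rate of the first procedure will be approximately 70% for the surgical cases". The catheter arm is assumed to succeed less often, at "35% to 40% for the PCA cases". Table 1 is titled "Anticipated results for different success rates of first PCA procedure". It gives power of 99%, 84% and 65% for PCA success of 35%, 45% and 50%, under a row for the chi-square test of the first procedure. The text gives 98% for the most favourable case.

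**What is listed as an outcome.** Assessment of recurrence names two primary outcomes: freedom from AF at 12 months and the occurrence of a second ablation. The Abstract names sinus rhythm at 6 and 12 months and the proportion requiring a second procedure. First-procedure success is in neither primary list and not among the secondary outcomes. It appears in the overall hypothesis at the start of Methods, as the reason why fewer second ablations are expected.

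**How the two are linked.** The Table 1 row "Fraction of second procedures in the two groups" reads 0.65, 0.55 and 0.50 for PCA against 0.30 for surgery.

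**What happens after a recurrence.**
- PCA arm: "it will be left to the investigator’s preference to refer the patients with PeAF recurrence to a second PCA procedure, surgical ablation, or switch"; the last of these options is rate control. The next sentence says that rate control is counted as a failed repeated procedure.
- Surgical arm, for patients whose recurrence is controlled by drugs: "it will be left to the preference of the investigator to continue the medical therapy or to refer the patient for a PCA". No counting rule follows.

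**The concern.** The second-procedure comparison is the only primary outcome on which the Statistical analysis section expects the arms to differ; it expects the final number in sinus rhythm to be equivalent. A reader will therefore take Table 1 as the power for second procedures. It is that only if failure of the first procedure and a second procedure are the same event for every patient. The treatment sections leave that step to the investigator, and the one rule that might restore the identity is written for one arm.

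Two things are at stake. Power for the outcome as listed may be lower than stated. Or, if the PCA rule is read as counting rate control as a second procedure, the outcome is defined differently by arm, and the test can favour surgery without any difference in first-procedure failure.

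**Working it through.** **Inputs.** 100 PCA and 50 surgical patients (Abstract and both treatment-group sections); surgical success 0.70 and PCA success 0.35, 0.45, 0.50 (Statistical analysis, Table 1); alpha 0.05, taken as two-sided because sidedness is not stated; no dropout, since none is given.

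**Step 1: reproduce the stated power.** With p1 and p2 the PCA and surgical proportions:

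- p̄ = (100·p1 + 50·p2)/150
- s0 = √[p̄(1 − p̄)(1/100 + 1/50)]
- s1 = √[p1(1 − p1)/100 + p2(1 − p2)/50]
- power = Φ[(|p1 − p2| − 1.96·s0)/s1]

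For failures 0.65 v 0.30: p̄ = 0.533, s0 = 0.0864, s1 = 0.0805, so power = Φ[(0.35 − 0.1694)/0.0805] = Φ(2.24) = 98.8%. The other columns give 83.8% and 65.1%. The stated 99/84/65% are reproduced. The 98% in the text is also compatible (98.0% with a continuity correction). The arithmetic is sound.

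**Step 2: find the hidden assumption.** 1 − 0.35 = 0.65, 1 − 0.45 = 0.55, 1 − 0.50 = 0.50 and 1 − 0.70 = 0.30. These are exactly the table's second-procedure fractions, so the share of recurrences counted as second procedures is 100% in both arms.

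**Step 3: reading A, the PCA rule only marks a rhythm failure.** Let q be the share of recurrences actually re-ablated, the same in both arms. The comparison is then q(1 − PCA success) v q·0.30. The article gives no q, so a range is shown. Power here is exact: the binomial probabilities of all outcomes of 100 and 50 patients in which the uncorrected Pearson chi-square has P < 0.05 are summed.

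| q (assumed) | PCA success 35% | 45% | 50% |
|---|---|---|---|
| 100% | 98.8% | 85.1% | 66.9% |
| 80% | 92.7% | 68.5% | 50.2% |
| 70% | 85.9% | 59.4% | 42.7% |
| 50% | 65.8% | 40.7% | 28.5% |

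Example by the Step 1 formula, q = 70% and PCA success 35%: 0.455 v 0.21, p̄ = 0.373, s0 = 0.0838, s1 = 0.0761, power = Φ[(0.245 − 0.1642)/0.0761] = Φ(1.06) = 85.6%, against 85.9% exact.

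The upper planning value of 40% PCA success has no column in Table 1. By the same formula it gives 94.6% at q = 100%, 82.6% at 80% and 73.7% at 70%.

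**Step 4: reading B, rate control counts as a second procedure in the PCA arm.** The PCA fractions stay at 0.65/0.55/0.50, and only the surgical 0.30 can fall. With an assumed 80% of surgical recurrences re-ablated it becomes 0.8 × 0.30 = 0.24, and exact power is 99.9% at 35% PCA success and 88.7% at 50%. Both are above the stated 99% and 65%.

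The cost is unequal counting. Suppose first-procedure failure is 50% in both arms, all PCA failures count, and 70% of surgical failures are re-ablated. The counted fractions are 0.50 v 0.7 × 0.50 = 0.35. The test at 0.05 is then significant about 43% of the time, almost always against PCA, although the first procedures perform equally.

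**The case against.** The strongest reply is the PCA counting rule itself. On a natural reading, all three options after a PCA recurrence count as repeated procedures, so 0.65/0.55/0.50 follow from the protocol's own definition. This stands as a possible reading. It means that a loss of power is not shown, and under it power is at or above the stated value. It does not make Table 1 right for the listed outcome, because the surgical section has no matching rule.

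Other points also have weight:

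- The Abstract's wording, *requiring* a second procedure, is close to first-procedure failure, and Methods states the link between the two openly. But Assessment of recurrence speaks of *occurrence*, and Statistical analysis of patients *receiving* repeated procedures. These are different endpoints unless every failure is re-ablated.
- Medical therapy in the surgical arm is offered only where drugs control the recurrence, so a single share q for both arms simplifies both sections. The table in Step 3 is an illustration, not a forecast.
- The lowest figures combine low assumed shares with the 45% and 50% columns, which lie outside the 35% to 40% planning range. At 35%, shares of 80% and 70% still give about 93% and 86%.

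A reader might infer that the trial is underpowered, or that its primary outcomes must be replaced. The documents support neither: they give no re-ablation share, the counting rule can be read two ways, and a single definition removes the problem while the current outcomes stay.

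**Conclusion.** The point holds as a mismatch between the powered endpoint and the listed outcomes. It is certain that 99/84/65% belongs to first-procedure success, that this is not a listed outcome, and that the table's second-procedure row assumes 100% conversion in both arms, which the treatment sections do not require.

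The consequence depends on how the PCA rule is read. Under reading A, power for actual second ablations falls to about 93/69/50% at an assumed 80% re-ablated in both arms, or 86/59/43% at 70%. Under reading B, power is not lost, but the outcome is counted differently by arm and the comparison is biased against PCA; in the illustration the test is significant about 43% of the time at equal first-procedure failure. These figures rest on the assumed shares, two-sided alpha 0.05 and no dropout. Both readings call for the same repair. The protocol should be changed, but the sample size need not be.

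**What to change.** 1. Relabel the Table 1 row as the fraction of first-procedure failures, and say that the stated power applies to that endpoint.
2. Define one counting rule for the second-procedure outcome and apply it identically in both arms. One option is first-procedure failure, meaning documented recurrence after the blanking period or a second ablation, analysed as the outcome that the 100 + 50 calculation supports. State whether the PCA rule on rate control marks a rhythm failure or a counted procedure. Reconcile *requiring* (Abstract), *occurrence* (Assessment of recurrence) and *receiving* (Statistical analysis).
3. If actual second ablation remains a primary outcome, state its power over a range of explicitly assumed re-ablation shares, as in Step 3.
4. Keep 12-month freedom from AF as an outcome, and say that it has no power figure.

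Cost: the stated power for second ablations may become less favourable. The trial is registered and recruiting, so the clarified definition should be recorded as a dated amendment and carried into the registration. No extra patients and no change to clinical management are needed; only the counting of outcomes changes.
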